#### Strategies to improve adherence to interventions

4.2.4

Participant compliance will be ensured in the following three points. (1) When recruiting subjects and signing the informed consent form, the researchers will explain in detail to the patients about the needs of the subjects during the observation period and establish a good relationship with the subjects to gain more trust. (2) During the trial, researchers will provide comprehensive education and guidance on disease management and preventive measures. This includes teaching patients about the nature of their condition, the importance of adherence to the treatment protocol, and strategies to prevent complications. By enhancing patients’ understanding and involvement in their own care, we aim to foster better compliance and active participation. (3) All participants in the intervention and control groups need to record participation in the intervention on a schedule. Ensure that the number of weekly interventions is achieved.

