## Trial design

3

A single-blind, pilot randomized controlled trial will be conducted to evaluate the preliminary efficacy and feasibility of mixed herb aromatherapy compared to standard care and CBT. This study will enroll ninety-nine post-stroke patients with PSD at the Second Rehabilitation Hospital of Shanghai. Prior to initiating rehabilitation, demographic details of all participants, including name, gender, age, education level, and medical history, will be collected. A centralized, web-based service provided by Research Randomizer (https://www.randomizer.org/) will be utilized to generate a randomization sequence, ensuring an even distribution of patients between the three groups: the non-active control group (receiving standard care), the aromatherapy group (undergoing daily aromatherapy inhalation), and the CBT group (receiving CBT sessions twice weekly) in a 1:1:1 ratio. The intervention will last for four weeks.

Primary feasibility outcomes will include recruitment rates, adherence to the intervention and completion rates. Recruitment rates will be monitored and documented weekly. Adherence will be tracked through participant logs, ensuring that each session is recorded. Completion rates will be calculated at the study’s conclusion.

Evaluation of intervention effectiveness will be conducted at three time points: before the intervention (baseline), immediately after the intervention (four weeks), and one month post-intervention, to assess the effectiveness of the treatments (see **Figure 1** for details).

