### Outcomes

4.3

The primary objective of this pilot RCT is to evaluate the feasibility of implementing mixed herb aromatherapy for treating post-stroke depression, and to determine if a full-scale RCT would be feasible. Feasibility outcomes, which will be the primary outcomes, include recruitment rates, adherence rates, and completion rates. Secondary outcomes will assess changes in depression, sleep quality, cognitive level, quality of life, and cerebral cortex activity in PSD participants after different interventions, evaluated using five rating scales, EEG testing, and fNIRS. Specifically, the details are as follows.

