#### Primary outcome measures

4.3.1

1. Recruitment rates: Recruitment rates will be calculated as the proportion of successfully recruited eligible participants within the specified period, documented weekly, and reported as a percentage of the total planned recruitment. A recruitment rate of at least 70% will be considered acceptable.

2. Intervention adherence: Intervention adherence will measure the proportion of participants who complete the intervention as planned. This will be tracked using participant logs that record the completion of each aromatherapy session, CBT session, and conventional treatment session. Adherence to each component will be reported weekly. An adherence rate of at least 80% will be considered acceptable. Additionally, feasibility outcomes will include the proportion of participants who complete all assessments as scheduled, assessing the practicality of integrating aromatherapy with existing treatments.

3. Assessment completion: Assessment completion will assess the proportion of participants who complete all scheduled assessments and follow-ups. This will be calculated and reported at the end of the intervention. A completion rate of at least 85% will be considered acceptable.

5. Safety Assessment: Safety will be evaluated through subjective and objective measures. Participants will report any discomfort or adverse reactions, and vital signs (heart rate, respiratory rate, blood pressure) will be monitored before and after each session. An adverse event log will document all incidents and management actions. Adverse reactions will be categorized as mild, moderate, or severe.

- Moderate: Noticeable symptoms that may interfere with daily activities but are not life-threatening, requiring medical intervention or short-term observation.

- Severe: Symptoms significantly impacting daily life, potentially life-threatening, requiring intensive medical intervention such as hospitalization or emergency medication.

An acceptable safety threshold is set at no more than 10% of participants experiencing moderate to severe adverse reactions.

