### Implementation

5.3

An independent statistician, separate from the participant enrollment and intervention administration processes, will generate the allocation sequence using Research Randomizer software (https://www.randomizer.org/), ensuring a balanced 1:1:1allocation to control group, CBT group or aromatherapy group. Trained research staff will manage participant enrollment, screening for eligibility without access to the allocation sequence, thus remaining uninformed of group assignments. Following consent, a distinct research team member will access the allocation via a secure system to assign participants to interventions, communicating these assignments to the intervention administrator responsible for treatment delivery. This administrator will be excluded from the enrolment and outcome assessment processes to avoid potential biases.

CBT will be delivered by the hospital unit’s psychotherapists. The aromatherapy intervention, utilizing traditional Chinese herbal powders, will be administered by physicians from the TCM Rehabilitation Department. These physicians have received specialized training in herbal powder aromatherapy, which includes:

Fundamentals of Aromatherapy: Understanding the principles and therapeutic benefits of aromatherapy using Chinese herbal powders.Application Techniques: Hands-on training on the proper preparation and application of herbal powders for aromatherapy.Safety Protocols: Comprehensive instruction on safety measures to prevent adverse reactions and ensure patient safety during the treatment.Patient Interaction: Techniques for effectively communicating with patients to enhance their comfort and cooperation during the therapy.

The training program is conducted by senior TCM specialists and certified aromatherapists, ensuring that the physicians are proficient in delivering the intervention effectively and safely. During the aromatherapy sessions, these trained physicians will accompany patients throughout the treatment to ensure proper and safe application.

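### The primary adherence outcome rests on logs that participants appear to fill in themselves, although staff deliver every session; near the 80% line, recording errors can change the verdict.

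*Protocol article*

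**What the plan says.** Section 4.3 makes adherence primary: "Feasibility outcomes, which will be the primary outcomes, include recruitment rates, adherence rates, and completion rates". Section 4.3.1 defines it at participant level, "Intervention adherence will measure the proportion of participants who complete the intervention as planned", and sets the line: "An adherence rate of at least 80% will be considered acceptable". Section 4.5 repeats the 80% among the criteria that help to judge whether a full trial is feasible.

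The data source is named twice. Section 3: "Adherence will be tracked through participant logs, ensuring that each session is recorded". Section 4.3.1: "This will be tracked using participant logs that record the completion of each aromatherapy session, CBT session, and conventional treatment session". Neither sentence says who makes the entries. Section 4.2.4 does, for a schedule kept in every group: "All participants in the intervention and control groups need to record participation in the intervention on a schedule".

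Delivery is by staff throughout. Section 4.2.2.1 assigns conventional rehabilitation to six certified professionals. For CBT, section 5.3 says "CBT will be delivered by the hospital unit’s psychotherapists". For aromatherapy it says that "these trained physicians will accompany patients throughout the treatment to ensure proper and safe application". Section 4.2.2.3 states that all patients are inpatients and that sessions are scheduled with staff. Section 4.3.1 also has vital signs taken before and after each session, as a safety measure.

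**The concern.** A self-kept log measures what was written down. A forgotten entry counts as a missed session, and an entry filled in afterwards counts as an attended one. The people keeping these logs are stroke inpatients with depression, and section 4.1.1.1 rules out only severe cognitive impairment. The schedule in section 4.2.4 is also one of the means of promoting adherence, so the same record would both encourage attendance and measure it.

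A direct observer is present at every session, but the protocol names no staff attendance record for adherence and nothing to check the logs against. At stake is a primary outcome with a fixed acceptance line: the result would reflect logging behaviour as well as attendance.

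**Working it through.** **The plan's own figures.** Section 4.5: 30 per group plus 10% gives 30 × 1.10 = 33, and 3 × 33 = 99, as stated. (Division by 0.90 would give 34 and 102, which has no bearing here.) The 80% line has no derivation to reproduce.

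**Where the line falls.** The protocol does not say whether the line applies per arm or overall. For one arm, 0.80 × 33 = 26.4, so 27 participants are needed: 27/33 = 81.8% passes and 26/33 = 78.8% fails. If 26 are truly adherent and one of the other seven back-fills enough entries to look adherent, the arm passes. If 27 are adherent and one forgets enough entries, it fails.

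**Inputs.** Aromatherapy is once a day for four weeks (4.2.2.3): 4 × 7 = 28 sessions. The number of sessions that makes a participant adherent is not given, so two readings are tried. Three quantities are assumptions: a, the true attendance per session; e, the share of attended sessions not logged; and f, the share of missed sessions logged as attended. Sessions are taken as independent.

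**Reading A: every session must be logged, and everyone truly attends all 28.** Adherent share = (1 − e)^28.
- e = 0.5%: 86.9%
- e = 1%: 75.5%
- e = 2%: 56.8%

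The 80% line is crossed at e = 1 − 0.80^(1/28) = 0.8%.

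**Reading B: at least 80% of sessions must be logged.** 0.80 × 28 = 22.4, so 23 of 28. Adherent share = P(X ≥ 23), with X binomial (28, a(1 − e)). The last column is the chance that at least 27 of 33 are counted as adherent.

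| a | e | a(1 − e) | Adherent share | Chance of ≥ 27/33 |
|---|---|---|---|---|
| 90% | 0 | 0.900 | 94.5% | 99.8% |
| 90% | 2% | 0.882 | 89.6% | 94.9% |
| 90% | 5% | 0.855 | 78.8% | 43.3% |
| 90% | 10% | 0.810 | 55.4% | 0.1% |
| 95% | 5% | 0.9025 | 95.0% | 99.9% |

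The last row shows that with higher true attendance the same 5% omission leaves the verdict unchanged.

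**Pooled session rate.** This is not the protocol's definition; it shows the two directions of error.
- Omission, a(1 − e): 0.85 × 0.90 = 76.5%, so a true 85% fails at 10% omission.
- Back-filling, a + (1 − a)f: 0.78 + 0.22 × 0.10 = 80.2%, so a true 78% passes.

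**The case against.** The strongest reply is that no single sentence says the patient-kept schedule is the outcome source. Sections 3 and 4.3.1 speak of participant logs, which could mean logs kept per participant. Section 4.2.4 speaks of a schedule, under a heading about improving adherence. This stands as a caution: the link is a strong inference, not an explicit statement. But section 4.2.4 is the only place that says who records attendance, and it says participants in all groups. If staff logs were meant, the three sections need rewording anyway.

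Second, there are safeguards. Section 4.3.1 has adherence reported weekly, section 4.2.4 wants the weekly number of sessions achieved, section 7.1 plans data quality audits, and section 9.2 has the trial manager check accuracy. These are general. None names an independent attendance source, and an audit cannot detect a forgotten or invented entry without one.

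Third, the error rates are assumed, and the verdict moves only when true adherence is near the line. This stands. Back-filling can produce a false pass only when the truth is below 80%, since a true 80% already passes.

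Fourth, a reader might infer that arms with more sessions to log are biased more. The documents do not support that in general. On a pooled rate the number of entries cancels out, and section 4.3.1 reports each component separately. It would follow only under a rule requiring all or most sessions, which the protocol does not state.

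Fifth, a condensed article may leave form design to other documents. That covers the layout of the form. It does not cover the data source, which the article itself states.

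**Conclusion.** The point holds as a weakness in the stated measurement method and should be corrected. A primary outcome with a fixed line is taken from a record that participants appear to keep, while a better source is present at every session.

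The size depends on two things the protocol does not give: the error rate and the per-participant rule. Under the assumptions above, about 1% omission is enough to turn a true pass into a fail if every session must be logged. About 5% is enough under a 23-of-28 rule at 90% attendance. At 95% attendance the same 5% changes nothing. Omissions that cluster in a few participants would lower the share under the every-session rule less than independent ones do.

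Two stronger readings are not supported. A reader might infer that this criterion alone decides whether a full trial is feasible; section 4.5 lists three criteria that help to determine it, and section 4.3.1 adds a safety threshold. A reader might also infer that the logs will be wrong by enough to reverse the result. The documents show only that they could be, in either direction, when true adherence is close to 80%.

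**What to change.** In sections 3, 4.2.4 and 4.3.1, state that adherence for the 80% criterion is taken from an attendance record signed at each aromatherapy, CBT and conventional session by the staff member who delivers it, in all three arms. Keep the participant schedule as a motivational aid and say that it is not the source for the criterion. The vital-sign entries already planned around each session can serve as a cross-check, since a staff record is not free of error either.

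The cost is a one-line sign-off per session by staff already present, a line on the case report form and the wording changes. No extra staff or visits are needed, and no treatment changes. The record shows the allocation, so it must be kept from the blinded outcome assessors, as the participant logs must be too.

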#### Relevant concomitant care permitted or prohibited during the trial

4.2.5

It is stated in the inclusion criteria that participants can not participate in other clinical trials and that there will be no treatment other than the usual treatments and interventions.

#### Provisions for post-trial care

4.2.6

N/a

### Outcomes

4.3

The primary objective of this pilot RCT is to evaluate the feasibility of implementing mixed herb aromatherapy for treating post-stroke depression, and to determine if a full-scale RCT would be feasible. Feasibility outcomes, which will be the primary outcomes, include recruitment rates, adherence rates, and completion rates. Secondary outcomes will assess changes in depression, sleep quality, cognitive level, quality of life, and cerebral cortex activity in PSD participants after different interventions, evaluated using five rating scales, EEG testing, and fNIRS. Specifically, the details are as follows.

#### Primary outcome measures

4.3.1

1. Recruitment rates: Recruitment rates will be calculated as the proportion of successfully recruited eligible participants within the specified period, documented weekly, and reported as a percentage of the total planned recruitment. A recruitment rate of at least 70% will be considered acceptable.

2. Intervention adherence: Intervention adherence will measure the proportion of participants who complete the intervention as planned. This will be tracked using participant logs that record the completion of each aromatherapy session, CBT session, and conventional treatment session. Adherence to each component will be reported weekly. An adherence rate of at least 80% will be considered acceptable. Additionally, feasibility outcomes will include the proportion of participants who complete all assessments as scheduled, assessing the practicality of integrating aromatherapy with existing treatments.

3. Assessment completion: Assessment completion will assess the proportion of participants who complete all scheduled assessments and follow-ups. This will be calculated and reported at the end of the intervention. A completion rate of at least 85% will be considered acceptable.

5. Safety Assessment: Safety will be evaluated through subjective and objective measures. Participants will report any discomfort or adverse reactions, and vital signs (heart rate, respiratory rate, blood pressure) will be monitored before and after each session. An adverse event log will document all incidents and management actions. Adverse reactions will be categorized as mild, moderate, or severe.

- Moderate: Noticeable symptoms that may interfere with daily activities but are not life-threatening, requiring medical intervention or short-term observation.

- Severe: Symptoms significantly impacting daily life, potentially life-threatening, requiring intensive medical intervention such as hospitalization or emergency medication.

An acceptable safety threshold is set at no more than 10% of participants experiencing moderate to severe adverse reactions.

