### Sample size and feasibility criteria

4.5

Since this study employs a novel mixed herbal aromatherapy intervention, there is no prior research directly comparable to reference. As this is a pilot RCT, the focus is on assessing the feasibility of the intervention rather than hypothesis testing. Therefore, the sample size estimation is not based on power analysis but according to rule of thumb.

Based on the guidance from Billingham et al. (49), a sample size of approximately 30 participants per group is considered appropriate for a pilot study. This sample size is justified by the need to gather preliminary data on feasibility outcomes, such as recruitment rates, adherence rates, and completion rates, and to ensure sufficient variability and precision in the estimates.

Taking into account 10% potential dropout rates, we will aim to recruit approximately 33 participants per group to ensure we have enough data for the feasibility analysis. This will result in a total sample size of approximately 99 participants across the three groups.

The predefined criteria for feasibility outcomes are:

- Recruitment rate of at least 70%: This is considered a reasonable and achievable target for pilot studies to ensure adequate participant recruitment.

- Adherence rate of at least 80%: This reflects a high level of participant engagement and compliance with the intervention protocol, which is crucial for obtaining reliable data.

- Completion rate of at least 85%: This indicates that the majority of participants complete the study, ensuring data integrity and minimizing the impact of dropouts on the study results.

These criteria will help determine the feasibility of conducting a full-scale RCT.

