#### Primary outcome analysis: feasibility metrics

8.1.1

Recruitment, adherence, and completion rates will be the focus, analyzed descriptively to provide insights into the practical implementation and scalability of the intervention. Each metric will be reported as a percentage:

- Recruitment rate: Proportion of eligible participants who were successfully recruited.

- Intervention adherence: Proportion of participants who adhered to the intervention throughout the study.

- Assessment completion: Proportion of participants who completed all assessments and follow-ups.

- Safety assessment: Safety will be evaluated through subjective and objective measures, including monitoring vital signs and documenting adverse reactions.

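### The 70% recruitment criterion has two conflicting denominators, and the 85% completion criterion is timed before the follow-up it counts

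*Protocol article*

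**What the plan says.** **Recruitment.** Section 4.3.1 (Primary outcome measures) begins: "Recruitment rates will be calculated as the proportion of successfully recruited eligible participants within the specified period". The same sentence then has the rate "documented weekly, and reported as a percentage of the total planned recruitment". The criterion follows: "A recruitment rate of at least 70% will be considered acceptable". Section 8.1.1, the analysis section for the same outcome, gives the definition as "Proportion of eligible participants who were successfully recruited" and states no threshold. Section 4.5 repeats the 70% criterion without naming a denominator, and sets planned recruitment at about 33 per group, about 99 in all.

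**Completion.** Sections 4.3.1 and 8.1.1 agree on what is counted: participants who complete all assessments and follow-ups. The criterion is 85%. On timing, section 4.3.1 says: "This will be calculated and reported at the end of the intervention". Section 3 (Trial design) differs: "Completion rates will be calculated at the study", a sentence that goes on to name the study's conclusion. Section 7.2 places the follow-up visit four weeks after the intervention ends.

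**Use.** Section 4.3 makes the feasibility measures the primary outcomes. Section 4.5 says the criteria will help decide whether a full-scale trial is feasible.

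**The concern.** Recruited over planned and recruited over eligible answer different questions. The first is accrual against a fixed target. The second is uptake among patients who could have joined. A trial that reaches its target by screening widely scores 100% on the first and may score low on the second; a trial with few eligible patients who mostly agree does the reverse. A single 70% cut-off cannot serve both unless the plan says which one it applies to. While that is open, the denominator could be settled after the counts are known, and the criterion would no longer be predefined.

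For completion, the rate as defined cannot be evaluated at the time section 4.3.1 sets, because one of the visits it requires has not yet taken place. If a figure is produced at week 4 anyway, it leaves out every loss between week 4 and the follow-up, yet would be compared with the same 85%.

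**Working it through.** **Planned recruitment.** Section 4.5 takes 30 per group and allows 10% dropout: 30 × 1.10 = 33 per group, and 33 × 3 = 99. This reproduces the protocol's figure, and 99 is the planned denominator used below.

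**Recruitment cut-offs.** Let R be the number recruited and E the number eligible.

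- Planned reading: R/99 ≥ 0.70. Since 0.70 × 99 = 69.3, it passes when R ≥ 70.
- Eligible reading: R/E ≥ 0.70, so it passes when E ≤ R/0.70.

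The readings disagree when R ≥ 70 and E > R/0.70 (planned passes, eligible fails), or when R ≤ 69 and E ≤ R/0.70 (planned fails, eligible passes). Even full recruitment fails the eligible reading once E exceeds 141: 99/141 = 70.2%, 99/142 = 69.7%.

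The protocol gives no eligible counts, so the values of R and E below are assumptions.

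| Recruited | Eligible | Of planned 99 | Of eligible |
|---|---|---|---|
| 72 | 150 | 72.7%, pass | 48.0%, fail |
| 66 | 90 | 66.7%, fail | 73.3%, pass |
| 99 | 160 | 100%, pass | 61.9%, fail |
| 99 | 120 | 100%, pass | 82.5%, pass |

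The last row shows that the readings can also agree.

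**Completion cut-off.** Assume 99 are randomised and all are in the denominator. Since 0.85 × 99 = 84.15, the criterion is met with 85 or more completers. A participant who misses an earlier assessment cannot later become a full completer, so the count after follow-up cannot exceed the count at week 4. The verdict can move only from pass to fail.

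The completer counts are again assumptions:

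- 90 at week 4, close to the planned 10% dropout: 90/99 = 90.9%, pass. 84 after follow-up: 84/99 = 84.8%, fail. The reversal takes 6 further losses among 90, or 6/90 = 6.7%.
- 89 at week 4: 89/99 = 89.9%, pass. 85 after follow-up: 85/99 = 85.9%, pass. Here the timing makes no difference to the verdict.

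**The case against.** **On recruitment**, the sentence in section 4.3.1 can be read as doing two things: calculating a rate among eligible patients, and reporting weekly accrual against target. On that reading it partly matches section 8.1.1. This is a fair point and softens the contrast. It does not remove the ambiguity, because the 70% follows directly after the planned-recruitment wording and section 4.5 does not say which quantity it judges. Section 4.5 defends the 70% as securing adequate recruitment, which suits accrual at least as well as uptake.

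**On completion**, the strongest reply is that there is only one definition. That is right: sections 4.3.1 and 8.1.1 count the same thing and section 3 times it consistently. A reader might infer that completion is defined in two competing ways, but the documents show one wrong time point in one sentence.

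**On how much turns on this**, a reader might treat the criteria as strict go/no-go rules. Section 4.5 says only that they will help determine feasibility, and section 8.1.1 analyses the rates descriptively. Section 8.1.1 also carries no threshold, so it would be wrong to say that 70% is written against both denominators.

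**On the size of the trial**, a reader might note that 70% of 99 falls short of about 30 per group and call that an inconsistency. The documents do not support this. Section 4.5 says that "a sample size of approximately 30 participants per group is considered appropriate for a pilot study", under a rule of thumb and without a power analysis. An acceptance threshold below the recruitment target is ordinary for a feasibility criterion. How strict it should be is a separate matter of judgement.

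**Conclusion.** The point stands in two parts of unequal weight.

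The main part is the recruitment denominator. It is a contradiction in the current text about a primary outcome with a predefined criterion, not a detail left to an analysis plan. The verdict can reverse in either direction; whether it does depends on eligible counts that the protocol does not give.

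The lesser part is the timing of completion in section 4.3.1. It conflicts with section 3 and with the outcome's own content. Used as written, it can only flatter the result against 85%. With 99 randomised and 90 complete at week 4, six further losses would be enough to change the verdict.

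A reader might infer that losses will concentrate after discharge. The protocol says that patients are inpatients and that hospital stay was considered in setting the follow-up (section 11), but it gives neither discharge timing nor a loss rate. The point does not depend on that inference. Nothing here changes the sample size.

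**What to change.** Before data are seen:

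- **Recruitment.** State one denominator for the 70% criterion and use it in sections 4.3.1, 4.5 and 8.1.1. The choice belongs to the authors; randomised over eligible would match the analysis section as it stands. Report the other quantity (on that choice, accrual against 99) separately and descriptively, with no threshold attached.
- **Completion.** In section 4.3.1, replace the end-of-intervention time point with calculation after the last one-month follow-up, in line with section 3. State that the denominator is all randomised participants and that this rate is judged against 85%.

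The cost is a few sentences of wording and a count of eligible patients from screening that is already planned (section 5.3). The reported rates may be lower than under the more favourable reading.
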